### Statistical Analysis

The primary analysis will be a completer analysis. Summary statistics (eg, frequencies, means, and medians) of the baseline variables will be calculated to assess the effectiveness of randomization. Treatment effects (mean differences in outcomes between the 2 groups at 3 and 6 months) will be estimated with mixed models. This model includes the interaction of treatment and time and allows adjustment for baseline scores. For each outcome measure, we will also adjust for age, sex, race, disease duration, and any variables that are statistically different from each other in unadjusted analyses (*P*<.10). A 2-tailed *P* value of .05 will be considered significant. All analyses will be conducted by a blinded statistician using SAS 9.3 (SAS Institute).

On the basis of previous studies performed by this research group within this population, we do not expect a large amount of missing data in the primary outcome measures and covariates. These data are obtained during in-person study visits. A research assistant is present during all study visits and checks forms for completion. When necessary, multiple imputation by chained equations will be used to impute missing variables.

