#### Randomization (Disease Activity Levels)

Participants will be randomized 1:1 using a publicly available Web-based randomization tool. Randomization will occur within categories stratified by disease activity, assessed by the CDAI: remission (≤2.8), low (>2.8-10), moderate (>10-22), and high (>22) [17].

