### Recruitment

The recruitment goal is 190 participants. Potential participants will be identified by searching for ICD-9 diagnosis codes for RA (714.x) in the Brigham Integrated Computing System scheduling database. Every week, study staff will generate lists of potential participants and prescreen patients via medical record review. Study staff will provide weekly lists to clinicians for their approval to contact the patients. Study staff will also be present in clinic during the busiest clinic sessions to remind HCPs of potential participants and to facilitate referrals. Every eligible participant will review the informed consent document approved by Partners Institutional Review Board, and written informed consent will be obtained by a trained research assistant. All study staff will complete training in HIPAA and Ethics in Human Subjects Research. Approximately 50.0% (95/190) will be randomized to receive the mobile app (intervention group). On the basis of attrition rates from previous studies, we expect ≥61.0% (122/190) of subjects to complete the study.

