### Sample Size Calculation

A total of 2920 RA patients were seen at the site of recruitment between April 30, 2013, and May 1, 2014. Of these patients, 1980 were prescribed at least one DMARD between April 30, 2013, and May 1, 2014, and approximately 60.00% (1188/1980) had moderate-to-high disease activity. From the 2013 Pew Internet Tracking Survey, we estimate that 50% of these patients (594/1980) own mobile phones [41]. Of these 594 individuals, we expect 80.1% (476/594) to meet the remainder of the inclusion criteria (≥18 years old, English speaking), and 40.0% (190/476) to agree to participate.

On the basis of previous studies examining differences in patient satisfaction, the expected difference between groups is 9.4 (SD 18.4) in TSQM scores [42,43]. No data exist regarding the expected difference in CDAI scores for this intervention. However, the minimal clinically important difference in CDAI scores is 12 [44,45]. On the basis of attrition rates from previous studies, we expect ≥61% (122/190, 64.2%) subjects to complete the study. Given a sample size of 122 subjects and an alpha level of .05, we will be able to reject the null hypothesis that the population means of the experimental and control groups are equal with probability (power) 0.80 to 0.99.

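### The primary analysis is restricted to completers although the plan counts on 36% of randomised participants, and allows up to 39%, not completing; the estimates may be biased if dropout relates to outcome differently by arm

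*Protocol article*

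**What the plan says.** The protocol article, Statistical Analysis, fixes the primary analysis set in one sentence: "The primary analysis will be a completer analysis". It does not define a completer, and neither this section nor any other names an analysis of all randomised participants. Treatment effects at 3 and 6 months are to come from mixed models with a treatment-by-time interaction, allowing adjustment for baseline score, with further covariates.

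On missing data, the same section says "we do not expect a large amount of missing data in the primary outcome measures and covariates". It explains that these data are collected at in-person visits, where a research assistant checks the forms. When necessary, "multiple imputation by chained equations will be used to impute missing variables".

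On attrition, Recruitment states "The recruitment goal is 190 participants" and "we expect ≥61.0% (122/190) of subjects to complete the study". Sample Size Calculation repeats this as "we expect ≥61% (122/190, 64.2%) subjects to complete the study" and bases power on the 122. Allocation is equal: "Participants will be randomized 1:1 using a publicly available Web-based randomization tool".

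**The concern.** Attending through to 6 months is decided after randomisation and may be affected by the assigned arm. Once the analysis set is chosen on such an event, randomisation no longer ensures that the two groups are comparable. Baseline adjustment helps only as far as the measured covariates explain who stays.

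The arms differ in ways that could affect who stays. Only the app arm has daily notifications and reminders, calls triggered by the flare algorithm, and calls after seven days without answers. These could hold participants in the study or tire them. Visits coincide with routine rheumatology visits, so attendance may also follow disease activity, which is itself measured by a primary outcome (CDAI). An influence of the app on retention could then appear as an effect on TSQM, PEPPI or CDAI, or could mask one.

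The planned mixed model could use the 3-month scores of people who later drop out. Restriction to completers removes them.

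**Working it through.** **Inputs from the protocol article.** 190 randomised 1:1, so about 95 per arm; 122 expected to complete, 61 per arm if dropout is equal; floor for completion 61%; TSQM difference 9.4 and SD 18.4 ("the expected difference between groups is 9.4 (SD 18.4) in TSQM scores"); two-sided alpha 0.05; stated power 0.80 to 0.99.

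**Step 1: the plan's own figure.** With 61 per arm:
- Standard error of the difference = 18.4 × √(2/61) = 3.33.
- Standardised effect = 9.4/18.4 = 0.51 SD.
- Power = 0.805 by the normal approximation and 0.799 by the noncentral t.

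The stated lower value of 0.80 is reproduced, which confirms that the design rests on analysing the 122. The upper value of 0.99 cannot be checked, because no SD is given for CDAI.

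**Step 2: how many are left out.**
- Planned: 190 − 122 = 68; 68/190 = 35.8%.
- At the floor: 0.39 × 190 = 74.1, about 74.

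**Step 3: when restriction biases the estimate.** In one arm, let d be the dropout proportion and g the completer mean minus the dropout mean. The completer mean then equals the full-arm mean plus d × g. With no true effect:

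bias = d(app) × g(app) − d(control) × g(control)

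This is zero if d and g are the same in both arms. It is non-zero if either differs while dropouts differ from completers. Two illustrations in TSQM points, before baseline adjustment, with d and g assumed:

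| Assumption | Bias |
|---|---|
| Equal dropout of 35.8% or 39%; g differs between arms by 5 points | 0.358 × 5 = 1.8; 0.39 × 5 = 2.0 |
| Dropout differs by 10 or 20 percentage points; g = 9.2 (0.5 SD) in both arms | 0.10 × 9.2 = 0.9; 0.20 × 9.2 = 1.8 |

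With a standard error of 3.33, a bias of 0.9 points raises two-sided type I error from 0.05 to about 0.06, and 1.8 points raises it to about 0.08. Larger assumed contrasts give proportionally larger bias.

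**Step 4: simulation of a baseline-adjusted completer analysis.** Assumptions: no true effect, 95 per arm, about 36% dropout in each arm, correlations of 0.5 to 0.7 between baseline, 3-month and 6-month scores, and dropout depending on the 3-month score through a logistic model.

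| Dropout mechanism (log-odds per SD of the 3-month score) | Absolute bias |
|---|---|
| Same in both arms (1 and 1) | 0 |
| Milder difference (0.5 against 1, or 0.5 in one arm only) | 0.03 to 0.08 SD |
| Stronger difference (1 in one arm only) | 0.07 to 0.14 SD |

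Type I error runs from about 5% with the same mechanism to about 14% in the worst of these cases. On the TSQM scale 0.14 SD is 0.14 × 18.4 = 2.6 points, or 0.14/0.51 = 27% of the design effect.

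**Step 5: does the plan contain a remedy?** A likelihood-based mixed model is valid under missing at random when participants with partial data enter it; a completer set shuts them out. Imputation is conditional, refers to missing variables and is not tied to non-completers. If it were meant to cover them, the primary analysis would not be a completer analysis. Neither provision changes the stated set.

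**The case against.** **Differential dropout is not shown.** Both arms have a population manager, an introductory call and calls at weeks 6 and 18, partly to keep participants engaged. Visits follow routine care in both arms, and the calls after seven silent days concern app surveys, not visit attendance. This stands: the document makes a difference between arms plausible and no more. If dropout works the same way in both arms and there is no true effect, the bias is zero.

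**The missing-data sentence need not contradict the attrition figure.** Its explanation concerns forms checked at attended visits, so it can be read as referring to skipped items, with imputation filling those gaps among attendees. A reader might infer that the section flatly contradicts the expected attrition and that the sentence should be deleted. The text does not support that. It is ambiguous and should be clarified.

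**The bias figures depend on assumptions.** This also stands. A reader might take a bias of 0.13 SD and a 13% false-positive rate as the expected damage. Those values are near the worst of the simulated cases and require dropout to depend on the score in one arm only. Nor should one expect the remedy to remove all bias. In such a simulation an analysis that uses the 3-month scores looks unbiased because dropout was generated from those scores and every dropout was assumed to have one. Participants lost before 3 months supply none.

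**The trial is called a pilot.** Barriers and Limitations uses the word, but the trial is powered for a between-group test at two-sided 0.05, and the Discussion says that it is designed to assess feasibility and efficacy.

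**Conclusion.** The concern holds. The article explicitly fixes a completer analysis as primary, while its own figures leave out 68 of 190 randomised participants (36%) as planned and about 74 (39%) at the floor. The higher figure is the most the plan allows, not what it expects.

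The TSQM, PEPPI and CDAI comparisons are no longer protected by randomisation and may be biased if dropout relates to outcome differently by arm. It would be too strong to say that the randomised comparison is lost: baseline scores and covariates are adjusted for, and the bias may be nil. The illustrative range is 0 to about 0.14 SD, with type I error from 5% to about 14%, against a design effect of 0.51 SD. It rests on the dropout mechanisms and correlations assumed above. The document does not allow the size or direction in this trial to be derived.

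The plan should still be changed before analysis, because the restriction affects every primary comparison and is cheap to remove.

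**What to change.** 1. Make the primary analysis one of all randomised participants in the arm assigned, using the same mixed model on all available 3- and 6-month data. State that it is valid under missing at random and does not correct dropout that depends on unobserved scores.
2. Add multiple imputation that covers non-completers, with stratum, baseline and 3-month scores in the imputation model, and a delta-adjusted version as sensitivity analysis.
3. Keep the completer analysis as supportive, and define a completer.
4. Clarify that the expectation of little missing data refers to forms at attended visits, and reconcile it with the expected attrition of 36% (up to 39%).

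The cost is wording and a little programming, with no new participants or data. The gain is mainly in validity. If all 95 per arm supplied outcomes, power for TSQM would be 0.94, but that is an upper bound, since no model recovers the full information in unobserved 6-month scores.

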### Outcome Measures

To assess patient satisfaction, the primary outcomes will be scores on the TSQM and PEPPI questionnaire at 6 months [21,22]. To determine the effect of the mobile app on RA disease activity, the primary outcome will be CDAI at 6 months [17].

The TSQM is a validated questionnaire that assesses medication satisfaction [21]. The different components of medication satisfaction are the following: side effects, effectiveness, convenience, and overall satisfaction. There are 14 questions, scored on a 5- or 7-point Likert scale. Responses to each question are assigned a score between 0 and 100, with 0 being extremely dissatisfied to 100 being extremely satisfied. The TSQM was initially validated in a national study of chronic disease, including patients with arthritis, asthma, depression, hyperlipidemia, hypertension, migraine, and psoriasis. It was subsequently validated in separate populations of patients with multiple sclerosis, cystic fibrosis, and coronary disease [30-32]. In one study, ceiling and floor effects were observed in the side effects domain [32]. Of note, if these effects are a problem, a separate score (TSQM-9) can be calculated, removing the 5 items in the side effects domain. This abbreviated score was shown to have good construct and convergent validity, along with high internal consistency and good test-retest reliability [33]. In a study of individuals with chronic illnesses including 25.6% (44/172) RA patients, representative scores on the TSQM were 77.1 (SD 25.2) for side effects, 61.6 (SD 24.16) for effectiveness, 66.1 (SD 17.1) for convenience, and 68.8 (SD 20.6) for overall satisfaction [34]. Although no studies have specifically examined the responsiveness of the TSQM in RA, a study of osteoarthritis patients revealed that perceptions of convenience, effectiveness, and overall satisfaction increased with treatment with a nonsteroidal anti-inflammatory drug [35]. The TSQM has also been used in clinical trials of RA patients to compare patient satisfaction with the effects of different DMARDs [36].

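### Three primary outcomes share an undivided .05 with no decision rule, and the TSQM score that counts as primary is not named

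*Protocol article*

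**What the plan says.** Under Outcome Measures, two questionnaires serve the satisfaction objective: "To assess patient satisfaction, the primary outcomes will be scores on the TSQM and PEPPI questionnaire at 6 months". A third primary serves the other objective: "To determine the effect of the mobile app on RA disease activity, the primary outcome will be CDAI at 6 months". The Abstract repeats this.

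Under Statistical Analysis there is one threshold: a two-tailed P "value of .05 will be considered significant". Nothing there orders the three outcomes, divides the level between them or says how many must succeed. Sample Size Calculation uses the same level: "Given a sample size of 122 subjects and an alpha level of .05", the null hypothesis is to be rejected "with probability (power) 0.80 to 0.99".

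On the TSQM score, Outcome Measures says: "The different components of medication satisfaction are the following: side effects, effectiveness, convenience, and overall satisfaction". Reference means and SDs are given for each component separately, and no component or total is named as the primary. Sample Size Calculation uses one difference (9.4) and one SD (18.4) for TSQM scores without naming a component. On the version, the text adds that "if these effects are a problem, a separate score (TSQM-9) can be calculated, removing the 5 items in the side effects domain", referring to ceiling and floor effects, with no criterion and no timing. For PEPPI the 10-item scale is described, with the remark that it showed a ceiling effect that the 5-item scale did not.

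**The concern.** Three outcomes are each entitled to be called the primary result, and each is judged at the full .05. Without a rule saying which results support which claim, one significant result among the three could be reported as success. The chance of that happening when the intervention does nothing is above 5%.

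The unnamed TSQM score adds a second gap. A reader cannot tell which number will be tested, and the planned power cannot be tied to any of the scores described. If the component is picked after results by arm are known, that is a further route to a chance finding.

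**Working it through.** **Inputs.** Two-tailed alpha .05 (Statistical Analysis and Sample Size Calculation). 122 completers with 1:1 allocation, taken as 61 per arm. TSQM difference 9.4, SD 18.4; CDAI difference 12, no SD given (Sample Size Calculation). Component SDs: side effects 25.2, effectiveness 24.16, convenience 17.1, overall satisfaction 20.6 (Outcome Measures). Correlations between outcomes are not given, so they are assumed below.

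**1. The plan's own power.** Standard error = 18.4 × √(2/61) = 3.332, and 9.4/3.332 = 2.821. Normal-approximation power = Φ(2.821 − 1.960) = 0.805; the t-test value is 0.799. This reproduces the lower figure of 0.80, so that figure uses the whole .05 on one test. The 0.99 fits the CDAI only if its SD is about 15.5 or less (assumed SD 15: 0.993; SD 20: 0.912).

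**2. Chance of at least one false positive, all nulls true.** For k independent tests at .05 it is 1 − 0.95^k. The correlated columns come from simulating two-sided z-tests with a common correlation (500,000 draws).

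| Reading | k | Independent | r = 0.3 | r = 0.5 | r = 0.7 |
|---|---|---|---|---|---|
| Satisfaction objective only (TSQM, PEPPI) | 2 | 9.75% | 9.6% | 9.0% | 8.3% |
| Three named primaries | 3 | 14.3% | 13.6% | 12.5% | 11.0% |
| Four TSQM components, PEPPI, CDAI | 6 | 26.5% | 24.0% | 20.7% | 16.4% |

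The last row is not what the plan states; it is taken up under the objection.

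**3. Is there slack to split alpha?** A Bonferroni level over three tests is .05/3 = .0167. TSQM power at 61 per arm then falls to 0.665 (t-test 0.653). Restoring 0.80 needs 81 per arm, or 162 completers: 162/0.642 ≈ 253 enrolled, or 162/0.61 ≈ 266, against 190 planned.

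**4. Would an all-must-succeed rule fit the stated power?** Joint power cannot exceed that of the TSQM, about 0.80. PEPPI has no stated power. The PEPPI comparison quoted under Outcome Measures (changes of +0.6, SD 5.2, and −0.91, SD 6.08) gives a difference of 1.51 and a pooled SD of √((5.2² + 6.08²)/2) = 5.66. Power at 61 per arm is then about 0.31. The stated range of 0.80 to 0.99 is consistent with testing each outcome on its own at .05.

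**5. Does the choice of TSQM score matter?** Holding the difference at 9.4 with 61 per arm, unadjusted t-test:

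| Component | SD | Power |
|---|---|---|
| Side effects | 25.2 | 0.53 |
| Effectiveness | 24.16 | 0.57 |
| Convenience | 17.1 | 0.85 |
| Overall satisfaction | 20.6 | 0.71 |
| Planning value, component not named | 18.4 | 0.80 |

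The planning SD equals none of the four.

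**The case against.** **Separate objectives.** The article ties TSQM and PEPPI to satisfaction and CDAI to disease activity. Read as two separate claims, the error is 5% for CDAI and at most 9.75% for satisfaction. The hypothesis in the Introduction couples better satisfaction with better disease management; if every primary had to succeed, there would be no inflation at all. Both readings are possible, but the article adopts neither, and the all-must-succeed reading sits badly with the stated power. On the separate-claims reading the satisfaction error is still nearly double the nominal level.

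**A 26% error rate.** A reader might infer this from the four TSQM components plus PEPPI and CDAI. The document does not support it: it never says that all four components will be tested as primaries. The figure also assumes independence, and falls to 16-24% at correlations of 0.7 to 0.3. It shows only what leaving the score open could permit.

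**Switching to TSQM-9 after seeing results.** A reader might infer this too. The remark is an aside about effects seen in an outside study and sets no timing. Such effects can be judged at baseline or on pooled blinded data, and the statistician is stated to be blinded. If components are tested separately, dropping the side-effects items leaves the other three scores unchanged, so the switch cannot simply be added on top of the six-test count. Freely picking the better of two versions (assumed correlation 0.8 to 0.95) would raise the error for the TSQM alone to 6.5-7.8%, and for the three primaries together to 15.6-16.7%, taking PEPPI and CDAI as independent. What stands is that no criterion is given.

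**Details left to the analysis plan.** That plan is not shown and may name the score or a rule. But the article itself fixes the undivided .05 and sizes the trial on it with nothing to spare, so a later split of alpha would contradict the stated power.

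**Pilot status.** The Discussion calls this a pilot and speaks of feasibility as well as efficacy. That tempers how firmly claims should be drawn, but the article still names primary outcomes, a significance level and power.

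**Conclusion.** The concern holds in a limited form. As written, three primary outcomes are each tested at an undivided two-tailed .05 with no decision rule. If any one suffices and all nulls are true, the chance of a false claim is up to about 14%: 14.3% if the tests are independent, 11-14% for assumed correlations of 0.7 to 0.3. If satisfaction and disease activity are separate claims, it is up to about 10% for satisfaction and 5% for CDAI.

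Separately, the TSQM primary score is not named and the planning SD matches none of the component SDs. The stated 0.80 therefore cannot be attached to a defined endpoint; with the quoted SDs, power runs from 0.53 to 0.85. Those SDs come from one outside study of mixed chronic illness and ignore baseline adjustment, which may recover some power.

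**What to change.** Before unblinding:

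- Name one TSQM score as primary, and one version each of TSQM and PEPPI. Any switch for ceiling or floor effects should follow a written criterion applied only to baseline or blinded pooled data.
- State one decision rule for the 6-month results. One option is a fixed sequence at .05 across the three primaries. Another is a fixed sequence of TSQM then PEPPI within satisfaction, with CDAI declared a separate objective and claim at .05.
- Report the other TSQM components, alternate versions and 3-month contrasts as secondary.
- Restate TSQM power for the chosen score. For overall satisfaction with SD 20.6, difference 9.4 and 61 per arm, it is about 0.71 unadjusted.

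**Cost.** About a paragraph, and no added patients under a fixed sequence. Later outcomes in a sequence are confirmatory only if the earlier test succeeds. Placing CDAI behind TSQM would block the only disease-activity primary in about 20-29% of trials even if the assumed TSQM effect is real (1 − 0.80 to 1 − 0.71). Declaring CDAI a separate claim avoids that, but controls error at 5% per objective, not across both. The restated power may be less favourable than the published range.
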